## Abstract

**Background:** Stroke is a leading cause of disability. Nonetheless, the care pathway for stroke rehabilitation takes partially into account the needs of chronic patients. This is due in part to the lack of evidence about the mechanisms of recovery after stroke, together with the poor knowledge of related and influencing factors. Here we report on the study protocol “Rehabilitation and Biomarkers of Stroke Recovery,” which consists of 7 work-packages and mainly aim to investigate the effects of long-term neurorehabilitation on stroke patients and to define a related profile of (clinical-biological, imaging, neurophysiological, and genetic-molecular) biomarkers of long-term recovery after stroke. The work-package 1 will represent the main part of this protocol and aims to compare the long-term effects of intensive self-rehabilitation vs. usual (rehabilitation) care for stroke.

**Methods:** We planned to include a total of 134 adult subacute stroke patients (no more than 3 months since onset) suffering from multidomain disability as a consequence of first-ever unilateral ischemic stroke. Eligible participants will be randomly assigned to one of the following groups: intensive self-rehabilitation (based on the principles of “Guided Self-Rehabilitation Contract”) vs. usual care (routine practice). Treatment will last 1 year, and patients will be evaluated every 3 months according to their clinical presentation. The following outcomes will be considered in the main work-package: Fugl-Meyer assessment, Cognitive Oxford Screen Barthel Index, structural and functional neuroimaging, cortical excitability, and motor and somatosensory evoked potentials.

**Discussion:** This trial will deal with the effects of an intensive self-management rehabilitation protocol and a related set of biomarkers. It will also investigate the role of training intensity on long-term recovery after stroke. In addition, it will define a set of biomarkers related to post-stroke recovery and neurorehabilitation outcome in order to detect patients with greater potential and define long-term individualized rehabilitation programs.

**Clinical Trial Registration:**
www.ClinicalTrials.gov, identifier: NCT04323501.

## Introduction

Stroke is a leading cause of death worldwide with an incidence of 150–300/100,000 per year. Despite the improvements in prevention and treatment of the acute phase, stroke remains the main cause of adult disability in Western Countries, with 40% of stroke survivors reporting problems in activities of daily living (1, 2). Currently, in Italy there are over one million people suffering from long-term disability after stroke (3). Nonetheless, the care pathway for stroke rehabilitation focuses mainly on the first period (a few weeks or a few months) after acute stroke, taking partially into account the needs of patients during the (short- and long-term) chronic phase. This is further stressed by the difficult access to rehabilitation and care after discharge. In our view this organizational model is also due to the lack of evidence about the mechanisms of recovery in the subacute and chronic phases of stroke together with the poor knowledge of related and influencing factors (3). Along these lines, within the framework of multidomain disability (sensorimotor, cognitive-behavioral, autonomic, and psychosocial) affecting patients with stroke it is necessary to define a number of clinical, functional, neurophysiological, neuroimaging, genetic-molecular, and psychological factors that correlate prospectively with long-term recovery and disability after stroke. This is in order to describe a profile of biomarkers that characterizes stroke patients with greater recovery potential, on which to base the development of innovative treatment protocols for long-term rehabilitation (4–8).

Here, we report the protocol of the study “Rehabilitation and biomarkers of stroke recovery” (ClinicalTrials.gov identifier NCT04323501), which is a single blind, randomized, controlled (parallel-group) trial consisting of seven work packages (WP). Its aim is to investigate the effects of a treatment protocol based on self-management for long-term neuromotor rehabilitation of stroke patients and to define a related profile of clinical-biological, imaging, neurophysiological, and genetic-molecular biomarkers of long-term recovery after stroke.

WP1 represents the interventional part of this protocol and compares the long-term effects of intensive self-rehabilitation vs. the usual rehabilitation care for patients with chronic stroke. Furthermore, it aims to define a set of neuroimaging (diffusion tensor imaging and functional magnetic resonance imaging) and neurophysiological biomarkers (motor evoked potentials and intracortical excitability measured by single and paired transcranial magnetic stimulation, somatosensory evoked potentials, and brain connectivity measured by electroencephalographic phase synchrony) related to the long-term outcome of neuromotor rehabilitation. WP2 aims to investigate cognitive plasticity mechanisms related to neuromotor recovery after long-term rehabilitation in patients with stroke. WP3 explores fatigue, body composition and walking issues in relation with long-term rehabilitation outcome after stroke. WP4 aims to define some psychological aspects, including distress, pain, and motivation, related to the long-term rehabilitation process and post-stroke outcome. WP5, WP6, and WP7 aim, respectively, to describe some issues about microbiota, microRNA expression, and oxidative stress phenomena associated with the mechanisms of post-stroke recovery in relation to long-term rehabilitation management (9).

## Methods and Materials

The study will be conducted at the Department of Neurosciences, Biomedicine, and Movement of Verona, University in Verona, Italy.

### Participants

As to eligibility for this protocol, the inclusion criteria are the following: age >18 years; multidomain disability as a consequence of first-ever unilateral ischemic stroke documented by computerized tomography scan or magnetic resonance imaging; and no more than 3 months since stroke onset; ability of patient and/or caregiver to understand the instructions provided for self-rehabilitation. Exclusion criteria are the following: inclusion in other trials; Mini Mental State Examination score <24/30 (10); drug addiction; and other neurological or orthopedic conditions limiting the inclusion in this protocol. Further eligibility criteria for WP2 are cognitive disability with adequate comprehension skills (people with limited attention span excluded). As to other additional eligibility criteria, WP3 will include patients with stroke who are able to walk and have adequate comprehension skills once they have reached the chronic phase of illness. An extra eligibility criterion for WP4 is the presence of painful conditions. The study does not include vulnerable populations such as prisoners, legally interdicted persons, or institutionalized people.

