### Randomization, Allocation Concealment, and Blinding

Prior to testing, eligible participants are randomly assigned in a 1:1 ratio to one of the two interventions of WP1: intensive self-rehabilitation (Group 1) vs. usual rehabilitation care (Group 2). The patients will be allocated to one of the two intervention arms according to a balanced (restricted) software-generated randomization scheme. Once the decision has been made, the investigator, who has determined whether a subject is eligible for the trial, is unaware of which group the subject would be allocated to (with the allocation contained in opaque sealed envelopes). Another investigator will check for correct patient allocation according to the randomization list. Investigators who assess outcomes are blinded to the intervention performed.

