### Interventions

Both types of interventions will last 1 year.

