### Data Analysis

Adequate descriptive statistics will be produced, including frequency, mean, median, standard deviation, interquartile range, and confidence intervals, for the demographic data and outcome measures at each time point. As to WP1, the comparison between groups, in terms of self-rehabilitation vs. usual care, with regard to the outcomes considered at each time point of the various evaluation times, will be performed using parametric (e.g., *t*-test, ANOVA) and/or non-parametric statistics, such as the Kruskal-Wallis test or the Mann-Whitney test, depending on the data distribution. Correlation and regression analyses will also be performed between neuroimaging data, neurophysiological variables, and clinical outcomes at different time points. As to the other WPs (2–7), comparisons between groups at different times will be assessed using parametric tests, such as the Student *t*-test and ANOVA, or non-parametric tests, such as the Kruskal-Wallis test and Mann-Whitney test, depending on the data distribution. For each variable considered, both longitudinally and transversely, correlation and regression analyses will also be performed. Moreover, for each WP we will perform longitudinal intragroup comparisons at different times by means of parametric tests, such as the *t*-test and ANOVA and/or non-parametric tests, such as the Friedman test and the Wilcoxon test, depending on data distribution. The statistical analysis will be performed using the Statistical Package for Social Science SPSS® version 26.0 software for Macintosh (SPSS Inc., Chicago, IL, USA). For all statistical tests, the significance level is set at *p* < 0.05.

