## Discussion

This trial will evaluate and follow up stroke patients from subacute stroke to the chronic phase, up to 1 year after stroke onset. It will deal with the effects of an intensive self-management rehabilitation protocol and a related set of biomarkers. In our view it will add some important pieces of evidence to overcome current conceptual limitations on long-term recovery models, upon which the usual care pathway of stroke rehabilitation is based. Another aspect that will be investigated by this study is the role of training intensity on long-term recovery after stroke, a point that will be further strengthened by the moral contract between patients and therapists (12). As suggested in the literature, intensity is a key element of stroke rehabilitation in order to achieve greater training effects (2, 27). In addition, a pattern of biomarkers related to post-stroke recovery and neurorehabilitation outcome will be useful to detect those patients with greater potential for recovery. Despite the fact that some of these biomarkers have been previously reported to offer information on stroke rehabilitation outcome, the prognostic relevance of their combination has never been explored to date and may be important for defining future long-term personalized medical rehabilitation programs. The possible main problems concerning the conduct of the study will be the number of patients enrolling, this being a single center study, the long follow-up duration (1 year), and the multifactorial/multimodal approach to evaluate patients; (that is, many different outcomes will be considered).

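### As written, WP3 selects patients on walking and comprehension in the chronic phase, after randomisation; if treatment changes who walks, its between-arm comparisons lose the protection of randomisation

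*Protocol article*

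**What the plan says.** The sequence has to be assembled from several sections of the protocol article.

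- **Entry (Participants):** "no more than 3 months since stroke onset".
- **Allocation (Randomization, Allocation Concealment, and Blinding):** "Prior to testing, eligible participants are randomly assigned in a 1:1 ratio to one of the two interventions of WP1".
- **Treatment (Interventions):** "Both types of interventions will last 1 year".
- **Follow-up (Discussion):** "This trial will evaluate and follow up stroke patients from subacute stroke to the chronic phase".
- **WP3 eligibility (Participants):** "WP3 will include patients with stroke who are able to walk and have adequate comprehension skills once they have reached the chronic phase" of illness.
- **WP3 outcomes (Outcomes):** the Multidimensional Fatigue Inventory (MFI), DEXA, and walking energetics and mechanics.
- **Analysis of WPs 2–7 (Data Analysis):** "comparisons between groups at different times will be assessed using parametric tests", or their non-parametric counterparts, at p < 0.05. Correlation, regression and within-group analyses are also planned.
- **Schedule (Table 1):** gait at T0, 3, 6, 9 and 12 months; MFI at T0 and 6 months; DEXA at 6 months only.

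The article does not define the chronic phase.

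**The concern.** Randomisation makes the arms comparable as they stand at allocation. A subset keeps that property if it is defined by something treatment cannot have altered. Walking ability after months of rehabilitation is not of that kind. The intervention is a motor programme, and 34 points of the primary outcome concern the lower limb. If the programme works as hoped, some patients in the self-rehabilitation arm will walk who would not have walked under usual care. They are likely to be marginal walkers. They enter WP3 from one arm only and lower that arm's average gait result.

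Comprehension is judged at the same late point and adds to the problem. Complete T0 measurements would not cure it, because the fault lies in who is compared.

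At stake is the reading of the WP3 arm contrasts: a programme that restores walking to more people could look weaker on gait than it is.

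**Working it through.** **1. Timing.** Entry at up to 3 months, randomisation before testing and 1 year of treatment place the chronic phase after allocation and within treatment and follow-up. On the wording of Participants, WP3 membership is therefore a post-randomisation variable.

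**2. Groups.** For WP1, Data Analysis names the contrast as self-rehabilitation against usual care. For WPs 2–7 it refers only to groups. The article defines no groups other than the two arms, so I read the WP3 tests as arm comparisons. That is an inference.

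**3. Size, model A.** The plan gives no WP3 figure to reproduce; its only sample size is for the FMA in WP1. All inputs here are assumptions. Locomotor ability is N(0,1) in controls, a patient walks above a threshold t, and treatment adds 0.40 SD for everyone. With φ the normal density and p the share walking:

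- mean of control walkers = φ(t)/p0
- mean of treated walkers = 0.40 + φ(t − 0.40)/p1

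With 60% of controls walking, t = −0.253:

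- controls: 0.3863/0.60 = 0.644
- treated: p1 = 74.3%; 0.40 + 0.3223/0.7432 = 0.834
- difference: 0.834 − 0.644 = 0.190 SD, or 47% of 0.40

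| Controls walking | Treated walking | Walkers-only difference | Share of 0.40 SD seen |
|---|---|---|---|
| 50% | 65.5% | 0.962 − 0.798 = 0.164 | 41% |
| 60% | 74.3% | 0.834 − 0.644 = 0.190 | 47% |
| 80% | 89.3% | 0.607 − 0.350 = 0.257 | 64% |

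This model attenuates the effect but does not reverse it.

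**4. Extreme case.** Suppose treatment only brings a further 14% of patients just to the threshold and changes nobody else. The treated walkers' mean is (0.60 × 0.644 + 0.14 × (−0.253))/0.74 = 0.474, and 0.474 − 0.644 = −0.17 SD.

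**5. Size, model B.** Here severity decides who walks and correlates r with the gait outcome. Treatment raises the walking share from p0 to p1 and separately shifts gait by a true effect. Write f(p) = φ(z_p)/p, where z_p is the normal quantile at p. The bias is r × [f(p1) − f(p0)], with f(0.50) = 0.798, f(0.60) = 0.644, f(0.70) = 0.497, f(0.75) = 0.424 and f(0.80) = 0.350.

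| Walking, control vs treated | r = 0.5 | r = 0.7 |
|---|---|---|
| 60% vs 60% | 0 | 0 |
| 60% vs 70% | −0.07 | −0.10 |
| 60% vs 80% | −0.15 | −0.21 |
| 50% vs 75% | −0.19 | −0.26 |

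At 60% vs 80% and r = 0.7, a true 0.2 SD effect appears as about zero (0.20 − 0.21), and a true 0.1 SD effect as about −0.1. A simulation with 1,000,000 patients per arm gave the same picture (−0.005 and −0.104).

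**6. Table 1 against Participants.** Gait and MFI are scheduled at T0. A set that is settled only in the chronic phase has no identified members at T0. Either the T0 measurements are taken more widely and the set is cut down later, or walking is in fact judged at T0. The article does not say which.

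**The case against.** Four points on the other side deserve weight.

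- **Timing is ambiguous.** Table 1's T0 entries may mean that walking is judged at T0, in which case the selection on later walking disappears. This stands as a reason to make the point conditional. It does not remove the point, because Participants says otherwise and the two places conflict.
- **WP3 is exploratory.** The Introduction calls WP1 the interventional part, and WP3's groups are not named as the arms. This limits the weight of the finding. Even so, significance tests are planned for WP3, and nothing marks them as non-randomised.
- **Gait can be measured only in walkers.** True for energetics and mechanics. It is not true of a fatigue questionnaire or a DEXA scan.
- **The bias needs an effect on walking.** Correct: that effect is the trial's hypothesis and is not established.

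A reader might infer that the WP3 comparison is certainly biased, or that a benefit will be reversed. The documents support neither. They give no walking rates, effect size or correlation. Model A only attenuates, and reversal needs either the extreme threshold case or a small true effect with a marked gain in walking. A reader might also carry the gait figures over to fatigue and body composition; a model of locomotor ability says nothing quantitative about those.

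Nor is this merely detail left to a fuller document: the entry rule and the tests are both stated here, and it is their combination that causes the difficulty.

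**Conclusion.** The point holds conditionally. On the wording of Participants, and reading groups as the arms, WP3 conditions a between-arm test on a state that the motor treatment aims to change. If treatment changes who can walk, a gait benefit may be attenuated: 41% to 64% of an assumed 0.40 SD effect would be seen with 50% to 80% of controls walking. Under model B the bias is about −0.07 to −0.26 SD for the unequal shares tried, enough to cancel or reverse a true effect of 0.1 to 0.2 SD in some settings. If walking shares are equal, that bias is zero. Every one of these inputs is assumed.

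The direction is uncertain for fatigue and body composition. The WP1 comparisons on the FMA, the Oxford Cognitive Screen and the Barthel Index are unaffected. The conflict between Participants and Table 1 needs resolving whichever reading was intended.

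**What to change.** 1. **Reconcile Participants with Table 1.** State when walking ability and comprehension are judged for WP3, and define the chronic phase if the term stays.
2. **Define the set for any between-arm WP3 comparison by T0 characteristics.**
   - MFI and DEXA: all randomised patients with adequate comprehension at T0, with no walking requirement.
   - Gait: either patients able to walk at T0, or all randomised patients with non-walkers given the worst rank. Specify worst rather than lowest, because a low energy cost of gait is not a poor result.
3. **Label** any comparison restricted to chronic-phase walkers as descriptive and non-randomised, and say in Data Analysis which groups are meant for WPs 2–7.

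The cost is wording in two sections plus some extra MFI and DEXA measurements in non-walkers. If the added scans are not acceptable, keep DEXA as planned and label its arm contrast descriptive. The T0-walker set will be smaller, and a rank analysis is harder to read than mean energetics. T0 gait and MFI are already scheduled, and the WP1 sample size does not change.

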### Recruitment

Subjects will be recruited among consecutive patients referring to the Neurorehabilitation Unit of the University Hospital of Verona in Italy. All participants will have to give their informed written consent to participate in the study.

### Randomization, Allocation Concealment, and Blinding

Prior to testing, eligible participants are randomly assigned in a 1:1 ratio to one of the two interventions of WP1: intensive self-rehabilitation (Group 1) vs. usual rehabilitation care (Group 2). The patients will be allocated to one of the two intervention arms according to a balanced (restricted) software-generated randomization scheme. Once the decision has been made, the investigator, who has determined whether a subject is eligible for the trial, is unaware of which group the subject would be allocated to (with the allocation contained in opaque sealed envelopes). Another investigator will check for correct patient allocation according to the randomization list. Investigators who assess outcomes are blinded to the intervention performed.

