Evaluation endpoints of WP4 include incidence of psychopathology (e.g., anxiety and depression) after stroke and related pain conditions, psychopathological issues, and coping strategies affecting adherence to rehabilitation programs, effectiveness of psychopharmacological and psychotherapeutic treatments in stroke patients, definition of specific psychological interventions supporting rehabilitation (17, 18). Accordingly, the outcomes considered are the Symptom Checklist-90 scale (19); the Eysenck Personality Questionnaire-R (20); the COPE scale (21); the General Self-Efficacy Scale (22); the Acceptance and Action Questionnaire-II scale (23); the Multidimensional Scale of Perceived Social Support (24); the Brief Pain Inventory-I scale (25).

The main endpoint of WP5 is to evaluate changes in microbiota related to post-stroke condition and recovery. Accordingly, the gut microbiota (GM) composition and changes will be evaluated at different time points. To identify bacterial species, present in GM, analysis of nine variable regions of 16S ribosomal RNA gene will be performed by next generation sequencing (NGS). Bioinformatical and statistical analyses will be conducted to relate gut microbiota signatures at different taxonomic levels to stroke rehabilitation conditions (25).

The main endpoint of WP6 is to evaluate the expression of microRNAs (miRNAs) related to post-stroke condition and recovery. Accordingly, in this study, the expression levels of circulating miRNAs (miR-9; miR-29a- 3p; miR-155-5p; miR-124; miR-146a; miR-210; miR-371-3p; miR-495-3p; miR-941; spike-in) will be analyzed at different time points starting from serum samples.

The main endpoint of WP7 is to evaluate the relationship between stroke, oxidative stress, and neuronal death issues. Accordingly, the following concentrations will be analyzed at different time points starting from plasma samples: glutathione disulphide ratio [GSH]/[GSSG]; nitrite/nitrate ratio [NO2^−^]/[NO3^−^]; and post-translational oxidative modifications of plasma proteins. Furthermore, the activation of STAT1 signaling will be evaluated in Peripheral Blood Mononuclear Cells (PBMC).

Evaluation time points for all WPs are reported in Table 1.

**Table 1 T1:** Evaluation time points.

	**T0°**	**T1°**	**T2°**	**T3°**	**T4°**
	**First week**	**3 months**	**6 months**	**9 months**	**12 months**
Informed consent	✓				
Inclusion and exclusion criteria	✓				
Clinical history	✓				
Fugl-Meyer Assessment	✓	✓	✓	✓	✓

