Oxford Cognitive Screen	✓	✓	✓	✓	✓
Barthel Index	✓	✓	✓	✓	✓
Volumetric analysis of the stroke	✓				
Side and site of stroke	✓				
DTI	✓				
fMRI	✓				✓
MEP and cortical excitability to TMS	✓				✓
SSEP	✓				✓
EEG	✓		✓		
MFI	✓		✓		
DEXA			✓		
Microbiota			✓		
Biochemistry and miRNA analysis	✓				✓
Usual care	✓	✓	✓	✓	✓
Intensive self-rehabilitation program	✓	✓	✓	✓	✓
Physiatric evaluation	✓	✓	✓	✓	✓
Video analysis and energetic cost of the gait	✓	✓	✓	✓	✓
Psychological evaluation scales	✓	✓	✓	✓	✓
Informed consent	✓	✓	✓	✓	✓

*DTI, Diffusion Tensor Imaging; fMRI, functional Magnetic Resonance Image; MEP, Motor evoked potential; SEP, Somatosensory evoked potential; TMS, Transcranial Magnetic Stimulation; EEG, Electroencephalography; MFI, Multidimensional Fatigue Inventory; DEXA, Dual X-ray Absorptiometry; miRNA, microRNA. °Time from the enrollment*.

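### Randomisation is placed before testing, so effort-dependent and self-reported T0 measures are post-allocation and may be taken when the patient knows the arm

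*Protocol article*

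**What the plan says.** The section on randomisation, allocation concealment and blinding opens with the order of events: "Prior to testing, eligible participants are randomly assigned in a 1:1 ratio to one of the two interventions of WP1". It adds that the investigator who decides eligibility does not know the coming assignment, "with the allocation contained in opaque sealed envelopes", and that "Investigators who assess outcomes are blinded to the intervention performed". The Introduction describes a "single blind, randomized, controlled (parallel-group) trial".

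Table 1 (Outcomes section) heads the T0 column as the first week, and its footnote defines the clock as "Time from the enrollment". In that column it ticks:
- informed consent and the eligibility check;
- "Fugl-Meyer Assessment", the OCS and the BI;
- the Multidimensional Fatigue Inventory (MFI) and the psychological scales;
- imaging and neurophysiology;
- the usual-care row and the row "Intensive self-rehabilitation program".

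The Data Analysis section compares the arms at each evaluation time. It also plans within-group comparisons over time in every work package, and correlation and regression analyses between imaging, neurophysiological and clinical variables. It names neither change from baseline nor baseline adjustment for the between-group comparison.

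**The concern.** A baseline should be fixed before anything that differs between the arms can act on it. Here the stated order is the reverse: patients are assigned and then tested.

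The two programmes are visibly different. One involves a moral contract with a therapist, a manual, a diary and daily exercises. The other consists of sessions prescribed by the patient's physiatrist. A patient told the arm knows what to expect, and a therapist delivering either programme knows it too. The FMA is scored on how fully the patient completes each item, so it depends partly on effort. The OCS also depends on performance, and the MFI and the psychological scales on the patient's own report. Once the arm is known, disappointment, enthusiasm or early practice could move these T0 values differently in the two groups.

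At stake are the uses of T0 as an untouched starting point. These are the check that the arms began alike, change from T0 within each arm, any adjustment for the T0 score, and the search for baseline predictors of recovery, which is a stated aim of the trial.

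**Working it through.** **1. The plan's own figure.** Inputs from the Sample Size section: difference 7, SD 11.6, power 80%, alpha 5% (two-sided assumed).

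- n per arm = 2 × (1.960 + 0.842)² × 11.6² / 7² = 2 × 7.851 × 134.56 / 49 = 43.1, rounded up to 44, so 88 in total. This agrees with the article.
- Power at 44 per arm: standard error = 11.6 × √(2/44) = 2.473; 7/2.473 − 1.960 = 0.870; power = 0.81.

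The order of testing and allocation does not enter this formula, so the correction leaves 88 unchanged.

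**2. The passages side by side.**

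| Source | What it fixes | What it leaves open |
|---|---|---|
| Randomisation section, first sentence | Assignment precedes testing | Which testing is meant; when the envelope is opened and the patient told |
| Table 1, T0 column | T0 measures and both treatment rows fall in the first week from enrolment | The order within that week |
| Blinding sentence | Outcome assessors are blinded | Patients and therapists are not covered |

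The first row is the only statement of order. T0 is the first testing occasion, so on the plain reading the T0 assessments follow assignment. That they also follow disclosure or the start of treatment is possible but not stated.

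**3. Which analyses are reached.** Suppose T0 in the self-rehabilitation arm is shifted by b points and later scores are not.

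- Unadjusted comparison at 12 months: the estimate is the difference in mean T4 scores. T0 does not appear, so the bias is 0.
- Difference between arms at T0: shifted by b.
- Within-arm change from T0 in that arm: shifted by −b.
- Between-arm difference in change from T0, if used: shifted by −b.
- Between-arm difference adjusted for T0 with common slope β, if used: shifted by −βb, which lies between 0 and −b for β between 0 and 1.
- Regressions on a T0 measure: affected only if that measure can be moved by effort or report.

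**4. Illustration on assumed values.** The article gives no value for b. The range below is assumed, and so is an analysis of change from T0 with SD 11.6 and 44 per arm.

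| Assumed b (points) | Expected difference, 7 − b | Power |
|---|---|---|
| 0 | 7 | 0.81 |
| 0.5 | 6.5 | 0.75 |
| 1 | 6 | 0.68 |
| 2 | 5 | 0.52 |
| 3 | 4 | 0.37 |

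A shift in the opposite direction would exaggerate the effect to 7 + b. The table shows only how such a shift would carry through; it does not estimate the shift.

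**The case against.** The strongest reply has five parts.

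- **Blinding.** A reader might infer that this is an open-label trial. It is not: the article calls it single blind and states that outcome assessors are blinded, which protects against rater bias at T0 as at later visits. This stands. It does not remove an influence that acts through the patient's own effort or answers.
- **Table 1.** A reader might infer from the treatment ticks that the programme is already running when the T0 FMA is taken. The column also holds consent and eligibility, which must precede randomisation, so it groups the week's events without ordering them. The treatment rows are also ticked at 12 months, when the one-year programmes end. This stands: the ticks leave early treatment possible but do not show it.
- **Disclosure.** Assignment is not the same as telling the patient, and the testing referred to is not expressly called baseline testing. This stands in part. Knowledge of the arm at T0 is a possibility, whereas post-allocation testing is the plain meaning of the sentence.
- **Condensed article.** The order of steps within a week is detail usually left to the full protocol. That would answer an omission, but here the article does state an order, and the order is the unfavourable one.
- **Reach.** It is tempting to extend the point to every baseline biomarker and to losses before T0. Stroke volume, stroke side and site, and diffusion imaging do not depend on effort or report, so the mechanism does not reach them. Because T0 includes consent and eligibility, no randomised patient can leave before T0 begins, and nothing in the article points to differential loss during that week.

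**Conclusion.** The point holds in a limited form. Followed as written, the plan produces a T0 baseline measured after allocation, in patients who cannot be blinded and who may already know their arm or have started their programme. Blinded assessors reduce the risk but do not remove it for the FMA, OCS, BI, MFI and psychological scales.

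The results exposed are T0 comparability between arms, within-group change from T0, any baseline-adjusted or change analysis, and regressions on those T0 measures. A reader might go further and conclude that the main comparison of FMA at 12 months is biased. If that comparison is made on unadjusted scores, it is not, and the article commits to no other form for it.

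The size of any effect cannot be derived from the documents. The conclusion rests on two readings: that the testing in the opening sentence includes the T0 assessments, and that patients learn their arm at or soon after assignment. The first is the natural reading; the second is plausible but unstated. The defect should be corrected because the remedy is cheap, not because harm to the results has been shown.

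**What to change.** Replace the opening phrase of the randomisation section with wording to this effect: consent, the eligibility check and the T0 assessments (at least FMA, OCS, BI, MFI and the psychological scales) are completed before the sealed envelope is opened. Then reconcile the treatment rows of Table 1 with that order, for example with a footnote separating the T0 assessments from allocation. If T0 testing is in practice already done before the envelope is opened, only the sentence and the table need correcting.

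The cost is that allocation waits until T0 testing is finished within the same week. There are no added visits, the content of either programme does not change, and the sample size stays at 88 evaluable patients.
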